#### Serum Metabolic Profile

Venous blood samples will be collected in the cubital fossa by a specialized professional after the participants have fasted for 3 hours following a standardized meal. Blood samples will be taken 3 times: before and immediately after the TUS+Aussie current session and immediately after HIIT. Each tube of blood collected will be left to stand at room temperature for 30 minutes. They will then be centrifuged at 1450 × g for 10 minutes (Sorvall ST 8 Benchtop Centrifuge; Thermo Scientific). The serum is divided into 3 aliquots in 1.5-mL microtubes using 5-mL disposable pipettes and stored immediately at −80 °C until further analysis. The serum samples will then be thawed at the UFSCar Department of Chemistry and sent for analysis using the hydrogen nuclear magnetic resonance technique. Serum glycerol, total cholesterol, very low–density lipoprotein, low-density lipoprotein (LDL), high-density lipoprotein, and triglycerides will be assessed. These will be measured using wet chemistry (except for LDL, which will be calculated using the Friedwald equation; ADVIA 1800; Siemens). The experimental procedures for this analysis will follow those described in the work by De Favari Signini et al [34] and Castro et al [35].

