#### Biochemical Blood Tests

Participants will be referred to a specialized clinic for blood collection. They will be instructed to fast for 10 hours before the test. The following will be collected: complete blood count, glycated hemoglobin (through high-performance liquid chromatography), fasting glycemia, insulin resistance (through enzymatic and chemiluminescent immunoassay), evaluation of the homeostatic model, C-reactive protein (through immunoturbidimetry), homocysteine (through chemiluminescence), total cholesterol, high-density lipoproteins, and LDLs and triglycerides (through the enzymatic method). The tests will be clinically relevant in the context of obesity and abdominal adiposity and may contribute to future studies to determine whether any changes occur in these variables after the intervention. The results will be reported by the unit’s physician and sent to the researcher.

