#### Secondary Outcomes

Secondary outcomes assess the impact on CAM, sleep quality, anxiety, depression, body image concerns, and blood biochemical variables (Table 2).

**Table 2 table2:** Primary and secondary outcomes of the study.

Variable		Description

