**Primary outcomes**		
	Abdominal subcutaneous adipose tissue (cm)	Ultrasound imaging [4,24]
	Body composition (kg; percentage and grams)	Dual-energy x-ray absorptiometry [30]
	Metabolic profile	Venous blood collection Hydrogen nuclear magnetic resonance [34,66]

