### Contributions to the Field

This study aims to guide health professionals to design more effective interventions, whether through combined therapy alone or associated with HIIT, for participants with overweight and grade-I or grade-II obesity by determining whether the combination of 2 therapies (TUS+Aussie current and HIIT) is more effective than just one of them in treating or preventing the disease. In addition, the results will contribute to knowledge about a nonpharmacological and noninvasive treatment for obesity and whether the proposed guidelines and interventions will be significantly different in the primary results (reduction in abdominal SAT and change in body composition and blood biochemical variables). In fact, if the results show significant differences between the proposed interventions, patients with obesity will benefit from the combination of 2 noninvasive and fast-acting therapies. In addition, previous studies lasting between 3 and 15 weeks were cited in this study. Thus, this pragmatic study will be able to verify the results of 5 weeks of intervention on the results described [22]. This study describes 10 sessions as this is the treatment protocol offered in most aesthetic clinics.

Previous studies have evaluated the isolated effects of TUS or combined therapies on body composition [4,9,11]; however, important methodological differences exist compared to this study. For example, Fonseca et al [4] investigated the effects of ultrasound in women only using a standardized model for demarcating the abdominal area, not considering individual anatomical variations. In addition, the intervention did not include the use of the Aussie current, and a manual massage protocol was applied after the ultrasound. Similarly, Taha et al [9] combined TUS with aerobic exercise in patients with nonalcoholic fatty liver disease; the exercises consisted of standardized walking sessions (30 minutes) controlled using the Borg scale (12-14), and the time of ultrasound application was not individualized based on abdominal area. Canela et al [11] studied the effects of combined ultrasound and Aussie current therapy associated with whole-body vibration; the sample was restricted to women with cellulite in the gluteal region and did not include a placebo group.

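### The primary metabolic profile is stated inconsistently as to assay and status, and it includes an LDL value calculated from post-meal, peri-exercise samples

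*Protocol article*

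**What the plan says.** **Assay.** In the protocol article, the Serum Metabolic Profile section has serum "sent for analysis using the hydrogen nuclear magnetic resonance technique". It then lists glycerol, total cholesterol, VLDL, LDL, HDL and triglycerides, and continues: "These will be measured using wet chemistry (except for LDL, which will be calculated using the Friedwald equation; ADVIA 1800; Siemens". Table 2, under primary outcomes, names only "Hydrogen nuclear magnetic resonance" for the metabolic profile.

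**In-session samples.** Blood is drawn "after the participants have fasted for 3 hours following a standardized meal". The timing is: "Blood samples will be taken 3 times: before and immediately after the TUS+Aussie current session and immediately after HIIT". Table 1 places the metabolic profile at weeks 1 and 5.

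**Fasting samples.** The Biochemical Blood Tests section covers total cholesterol, HDL, LDL and triglycerides, among other tests, by an enzymatic method. Of participants it says: "They will be instructed to fast for 10 hours before the test". Table 1 places the blood test at weeks −4, 0 and 6.

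**Status.** The Abstract, the Primary Outcomes section and Table 2 make the metabolic profile primary. The Secondary Outcomes section covers "CAM, sleep quality, anxiety, depression, body image concerns, and blood biochemical variables", and Table 2 lists the fasting lipids as secondary. The Discussion, under Contributions to the Field, refers to "primary results (reduction in abdominal SAT and change in body composition and blood biochemical variables".

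**The concern.** Two things are at stake.

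The first is what the primary outcome is. A reader of Table 2 expects an NMR result. A reader of the Serum Metabolic Profile section finds wet chemistry for every named analyte except LDL, which is calculated, and no NMR metabolite is named. Four lipids then stand in both a primary and a secondary set, and one sentence in the Discussion gives the secondary set primary status. A favourable fasting lipid result could be reported as primary on the strength of that sentence.

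The second is how in-session LDL is obtained. The Friedewald equation estimates VLDL cholesterol from triglycerides and subtracts it. Here it is applied after a meal, after the device and after intense exercise, when the ratio it assumes may not hold. The TUS+Aussie-only group does no HIIT, so any exercise-related distortion could fall on two arms and not the third, and could look like an LDL effect.

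**Working it through.** **1. The two lipid sets side by side**

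| | In-session metabolic profile | Biochemical blood tests |
|---|---|---|
| Status in Outcomes section and Table 2 | Primary | Secondary |
| Status in Contributions to the Field | Metabolic profile not named | Named among the primary results |
| Time since eating | 3 h after a standardized meal | 10 h fast |
| Weeks (Table 1) | 1 and 5 | −4, 0 and 6 |
| Assay in the Measures text | Wet chemistry; LDL calculated; NMR also mentioned | Enzymatic method |
| Assay in Table 2 | NMR only | None named |
| Lipids | Total cholesterol, VLDL, LDL, HDL, triglycerides | Total cholesterol, LDL, HDL, triglycerides |

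Four lipids appear in both columns. Two statements cannot stand as printed: the single assay in Table 2, and the primary status in the Discussion.

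**2. How calculated LDL depends on triglycerides**

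The article names the equation but does not print it. I assume the usual form in mg/dL:

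LDL(calc) = TC − HDL − TG/5

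Since TC = LDL(true) + HDL + VLDL,

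LDL(calc) − LDL(true) = VLDL − TG/5.

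For an acute change, the error in the LDL change is therefore ΔVLDL − ΔTG/5. Let VLDL cholesterol move by a share *k* of what the formula assumes, so that ΔVLDL = *k* × ΔTG/5. Then:

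error = −(1 − *k*) × ΔTG/5.

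The documents give no triglyceride changes, so the values of ΔTG below are assumptions:

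| ΔTG (mg/dL) | *k* = 0 (TC and HDL fixed) | *k* = 0.5 | *k* = 1 (VLDL in proportion) |
|---|---|---|---|
| 20 | −4 | −2 | 0 |
| 50 | −10 | −5 | 0 |
| 80 | −16 | −8 | 0 |

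For example, with ΔTG = 50 and *k* = 0: −(1 − 0) × 50/5 = −10 mg/dL. With *k* = 1, total cholesterol rises by 10, the formula subtracts 10, and calculated LDL does not move. For a fall in triglycerides the signs reverse.

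**3. Whether this could differ by arm**

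All arms have the standardized meal and a pre-device sample, so under randomization the meal alone does not produce an arm difference. The device is active in two arms and switched off in the placebo arm. HIIT is given in two arms and not in the TUS+Aussie-only group. A triglyceride shift caused by either could therefore differ between arms, and so could the error in calculated LDL.

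**The case against.** The strongest defence is that the two lipid sets answer different questions. Table 1 has separate rows and weeks for them, and the Statistical Methods section has separate factors: moment (before and after the intervention) and time (within the session). The Abstract, Outcomes section and Table 2 agree on which set is primary. Measuring the same lipids as an acute response and as a fasting change is legitimate. This stands. A reader might infer that the trial may freely choose between fasting states; the documents do not support that. The opening comes only from the Discussion sentence, which may be no more than loose wording.

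On the assay, the text does assign the named analytes to wet chemistry, and NMR may be meant as a wider metabolite panel. The serum is split into three aliquots, which would allow both. That is plausible, but the article does not say it, and Table 2 still omits the only assay given for the named analytes.

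On LDL, two stronger readings are tempting. One is that every triglyceride change produces an opposite LDL change. The algebra shows this only when total cholesterol does not move with triglycerides; with proportional movement the error is zero. The other is that the trial itself predicts acute triglyceride differences between arms. The Implications section predicts lipolysis, seen in serum glycerol, and oxidation of serum fatty acids; its reference to lipid profile is general and names no triglyceride change.

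Finally, making the fasting samples the primary lipid outcome would redesign the trial's acute hypothesis while data are being collected. The inconsistency does not require that.

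**Conclusion.** The point holds in a limited form. The assay in Table 2 conflicts with the Serum Metabolic Profile section, and the Discussion conflicts with the Abstract, the Secondary Outcomes section and Table 2 over the status of blood biochemistry. Four lipids are affected.

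In-session calculated LDL is a weak primary measure because it rests on a triglyceride term applied after a meal, after the device and after exercise. The size of any distortion cannot be derived from the documents. Under the assumed triglycerides/5 coefficient, and with VLDL cholesterol moving anywhere between not at all and in full proportion, a 50 mg/dL triglyceride rise gives an error between −10 and 0 mg/dL. That an arm difference in LDL will arise this way is not shown, only that it could.

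Subcutaneous fat thickness, body composition and serum glycerol do not depend on calculated LDL. The matter should be corrected before analysis, but it does not undermine the trial as a whole.

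**What to change.** 1. In Table 2, name wet chemistry as the assay for glycerol and the listed lipids, and state in Table 2 and in the Serum Metabolic Profile section what the NMR analysis yields.
2. Do not report LDL calculated from the in-session samples as a primary outcome. Take LDL from the 10-hour fasting samples already scheduled.
3. Keep the other in-session analytes (glycerol, total cholesterol, VLDL, HDL, triglycerides) as the primary acute profile and the fasting lipids as secondary. Correct Contributions to the Field to match the Secondary Outcomes section.

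The cost is wording in three places and the loss of an in-session LDL result. All samples needed are already scheduled in Table 1. Item 2 takes one analyte out of a primary outcome, so it should be recorded with a date before analysis begins; the Results section places the start of analysis after the last reassessment.

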#### CAM Measurement

To ensure the quality of the electrocardiogram (ECG) signal collection, the recommendations suggested by Catai et al [36] will be followed. All participants will be instructed to have a regular night’s sleep the night before, avoid alcoholic and caffeinated drinks, refrain from strenuous physical exercise at least 24 hours before and on the day of the assessment, and avoid heavy meals up to 2 hours before the assessment. All procedures will be explained beforehand to familiarize participants with the equipment and the assessor. The experiment will be carried out in the afternoon in a quiet room with the minimum number of people in the Cardiovascular Physical Therapy Laboratory, with controlled temperature and relative humidity (22-23 °C and 40%-60%, respectively) [36]. Before starting data collection, the participants will rest for 10 to 15 minutes to stabilize the signals [36]. After this, they will remain in the supine position for 15 minutes and then perform active postural change, remaining in the orthostatic position for 15 minutes. Participants will be instructed to breathe spontaneously and not to move or speak during the experiment.

RR intervals will be captured via ECG (Bio Amp FE132; ADInstruments) from the modified shunt in the fifth left intercostal space lead. In addition, respiratory movements will be captured using a respiratory belt positioned around the participants’ chest (Marazza) to obtain the respiratory rate during the test. Arterial pressure (AP) will be measured continuously beat to beat using a photoplethysmograph (Finometer PRO; Finapres Medical Systems) on the middle finger of the right hand. RR interval signals, AP, and respiratory movement will be sampled at 1 kHz using a commercial acquisition device (PowerLab 8/35; ADInstruments).

Classic linear indexes of HR variability will be calculated in the time and frequency domains. The indexes calculated in the time domain will be the SD of the NN interval, which represents sympathetic and parasympathetic modulation together, and the square root of the mean of successive NN intervals, which indicates parasympathetic modulation [37,38]. After detecting the QRS complex on the ECG, the apex of the R wave will be identified using parabolic interpolation. The heart period (HP) will be calculated as the temporal distance between 2 consecutive parabolic apexes. A stable sequence of 256 beats (for systolic AP [SAP] and HP) will be chosen in the supine and orthostatic positions, and if isolated ectopic beats are present, they will be linearly interpolated [39]. From these 256 points, the mean and variance of the HP and the mean and variance of the SAP will be calculated in the time domain.

The variability parameters of the HP and SAP will be evaluated according to the autoregressive model [39]. The spectral components will be broken down into LF (from 0.04 to 0.15 Hz) and high frequency (>0.15 to 0.4 Hz) reported in absolute units. The power of the spectral components will be expressed in absolute units or normalized units [38].

Symbolic analysis will be used to evaluate the HP and SAP series as defined in the study by Porta et al [40]. This technique is based on the 6-level uniform quantization procedure applied to HP and SAP series, which transforms series into sequences of symbols (from 0 to 5) from which patterns of 3 consecutive symbols will be constructed [41]. All possible patterns will be grouped without loss of information into families according to the number and type of variations between subsequent symbols: (1) 0V pattern—all symbols are the same; (2) 1V pattern—2 underlying symbols are the same, and the rest are different; (3) 2LV pattern—the 2 variations between adjacent symbols have the same sign; and (4) 2UV pattern—the 2 variations between adjacent symbols have opposite signs. Percentages of patterns within each experimental session were evaluated and denoted using 0V%, 1V%, 2LV%, and 2UV%, respectively. The 0V% index will be understood as a marker of sympathetic modulation when calculated in the HP and SAP series, and the 2UV% index will be understood as an index of vagal modulation when calculated in the HP series [40,42,43].

The baroreflex system will be evaluated through cross-spectral analysis using a bivariate autoregressive parametric approach [44]. The time-series relationships between AP and HP will be represented as coherence, phase, and transfer function gain. The coherence function shows the degree of association between the HP and SAP variabilities [44,45]. Its values range from 0 to 1, where values closer to 1 represent better coupling between the signals. The phase function represents the temporal relationship between the series (ie, the delay between the change in the SAP signal resulting from the heartbeat) and will be evaluated in high frequency and LF [44].

#### Sleep Quality

Sleep quality is assessed using the Pittsburgh Sleep Quality Index for sleep quality, adapted for Brazilians by Bertolazi et al [46]. It is a reliable instrument (intraclass correlation coefficient=0.65) [47] that assesses 7 components of sleep: subjective quality, sleep latency, sleep duration, sleep efficiency, sleep disturbances, medication use, and daily dysfunction. For each component, the score ranges from 0 to 3, and the sum yields a maximum score of 21. Scores of >5 indicate poor sleep quality.

#### Anxiety, Depression, and Stress

Anxiety and depression will be assessed using the Hospital Anxiety and Depression Scale validated for Brazilians [48]. It consists of 14 items divided into 2 domains (depression and anxiety) with 7 items each. The items are scored on a 4-point Likert scale (from 0 to 3), resulting in total scores ranging from 0 to 21 for anxiety and depression. The cutoff points indicating moderate to severe symptoms are ≥8 for the anxiety domain and ≥9 for the depression domain.

Stress is assessed using the Depression, Anxiety, and Stress Scale, which measures the levels of these disorders based on behaviors in the previous 7 days. The items use a 21-question Likert scale, which has been translated into Brazilian Portuguese, to rate the frequency or severity of the participants’ experiences on a 4-point scale [48].

#### Body Image

The Body Shape Questionnaire, validated for the Brazilian population [49], is a self-administered questionnaire consisting of 34 items designed to measure satisfaction and concerns about body shape. It is organized on a 6-point scale: 1=*never*, 2=*rarely*, 3=*sometimes*, 4=*frequently*, 5=*very frequently*, and 6=*always*. The score is the sum of the answers, where ≤110 points indicates no concern, ≥111 to ≤138 points indicates mild concern, ≥139 to ≤167 points indicates moderate concern, and >168 points indicates serious concern [49]. This questionnaire helps assess potential changes in satisfaction or concern about the body after the proposed treatment.

#### Biochemical Blood Tests

Participants will be referred to a specialized clinic for blood collection. They will be instructed to fast for 10 hours before the test. The following will be collected: complete blood count, glycated hemoglobin (through high-performance liquid chromatography), fasting glycemia, insulin resistance (through enzymatic and chemiluminescent immunoassay), evaluation of the homeostatic model, C-reactive protein (through immunoturbidimetry), homocysteine (through chemiluminescence), total cholesterol, high-density lipoproteins, and LDLs and triglycerides (through the enzymatic method). The tests will be clinically relevant in the context of obesity and abdominal adiposity and may contribute to future studies to determine whether any changes occur in these variables after the intervention. The results will be reported by the unit’s physician and sent to the researcher.

#### Perimetry

The waist-to-hip ratio is a calculation based on waist and hip circumference measurements [50]. It is often used to assess the risk of developing diseases such as high cholesterol, diabetes, and high blood pressure [50]. The presence of these cardiovascular risk factors, associated with increased abdominal fat, leads to a high risk of diseases such as myocardial infarction, stroke, and hepatic steatosis and mortality. The values considered normal for male and female individuals are <0.95 and <0.80 cm, respectively [50]. The waist-to-height ratio, on the other hand, is an index that assesses health risks by indicating the proportionality between waist circumference (a possible indicator of central fat accumulation) and height, suggesting a risk of cardiovascular or metabolic diseases [51]. Values of <0.5 cm indicate a lower risk of diseases, whereas values of >0.5 cm indicate a higher risk [51]. The measurements will be taken with the participant standing upright wearing light clothing. The waist circumference is measured as the average distance between the last floating rib and the anterior superior iliac crest [52]. The hip circumference is measured around the widest part of the buttocks at the level of the greater trochanter of the femur [52]. All measurements will be taken twice using an inextensible tape measure, and if there is a difference of 3 cm, a third measurement is taken for both waist and hips [52]. The ratio between the measurements is calculated as the waist circumference divided by the hip circumference.

Neck circumference is measured using an inextensible tape measure perpendicular to the longitudinal axis of the neck over the thyroid cartilage [53]. Participants will be in an anatomical position, either standing or sitting, with their head in the Frankfurt plane and their shoulders relaxed and in inspiratory apnea [53]. The cutoff points for overweight and obesity will be 37 cm for men and 34 cm for women [54]. The values above these cutoffs indicate increased cardiovascular risk factors [54].

#### Physical Activity

All participants will be characterized by their level of physical activity at a single point in time (before the intervention). The long version of the International Physical Activity Questionnaire is used. The International Physical Activity Questionnaire is a validated instrument for the Brazilian population that assesses the level of physical activity. It has 27 questions related to physical activities performed in a week at different intensities—light, moderate, and vigorous—lasting at least 10 minutes continuously. The questions cover 4 dimensions: work, transportation, domestic activities, and leisure, as well as the time spent seated [55]. The score is calculated by adding the workload for each subitem separately [55]. This questionnaire helps classify the level of physical activity before the proposed interventions.

Before the intervention, a treadmill ergometric test is conducted using the Ellestad protocol [56] for clinical cardiological assessment and to assist in prescribing HIIT. The test is interrupted according to the criteria recommended by the third version of the Sociedade Brasileira de Cardiologia ergometry guidelines [57]. The original Borg scale is used to assess the participants’ perception of dyspnea, lower-limb fatigue, and angina during exercise. This scale ranges from 0 to 10, where 0 is no dyspnea and 10 is the most intense dyspnea, fatigue, and angina [58]. The following determines the presence of maximum or peak effort: peak HR (HR_peak_)≥85% of that predicted for age (220 – age) and Borg perceived exertion of 18 on a scale from 6 to 20 (patient exhausted) [59].

